### Efficacy Endpoints

[Secondary Endpoints]

1) Frequency of hearing loss episodes (number of occurrences per year)

2) Highest measurement of auditory threshold shift at a hearing loss episode (dB)

Definition of hearing loss episodes: Hearing loss episodes with subjective symptoms and episodes detected as audiometric data will be counted as hearing loss episodes in this trial. Concerning audiometric data, audiometric testing of four different frequencies for right and left ears will be performed, and the average of measurements obtained at five recent time points will be defined as the baseline. A change of 10 dB or more observed in the testing period including the screening phase will be identified as an episode. The period from the beginning of the episode until the condition returns to the baseline will be counted as one episode. Episodes observed in left and right ears or in different frequencies concurrently will be considered as separate episodes.

3) Frequency of dizzy spells (number of occurrences per year)

Dizzy spells in which the subject is conscious are to be counted.

4) Maximum amplitude (°/sec) and maximum frequency (cycle/sec) of nystagmus in a hearing loss episode

5) Percentage of cases in which increase in hearing threshold was observed during remission in the observation period (comparison of measurements at the end of Phase I and the end of Phase II)

6) Improvement in threshold during remission

7) Shorter duration of hearing loss episodes

8) Alleviation of symptoms of dizziness/vertigo

Changes in total scores of the Dizziness Handicap Inventory from Phase I to Phase II

9) Percentage of cases in which equilibrium exacerbated during remission in the observation period (comparison of measurements at the end of Phase I and the end of Phase II)

[Exploratory Endpoints]

1) Reduction in endolymphatic hydrops (MRI findings)

2) Inhibition of goiter or thyroid enlargement

3) Cell biological changes in thyrocytes detected by cytology tests

4) Comparison of results of in vitro efficacy evaluation of inner ear cells derived from PDS-specific iPS cells and of clinical evaluation

5) Deviation from threshold value for frequency of abnormalities of auditory brain stem responses and for pure-tone audiometry

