### Posturography

The principal investigator or subinvestigator will perform posturography during the screening phase (V0), Phase I (V1, V3, and V4), Phase II (V5, V7, V8, V9, V10, V11, and V12), the follow-up phase (V13), and at discontinuation, and record the results on the electronic case report forms.

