## Statistical Analysis of Efficacy

Assessment of efficacy in this trial is regarded as a secondary objective. With regard to continuous endpoints, summary statistics of changes or percentage changes based on actual measurements and from baseline at each point in time will be calculated for each dosage arm. A one-sample *t*-test will be used for comparison between actual measurements and baseline values at each point in time for each dosage arm. The two-sided 95% confidence interval for average change for each dosage arm will then be estimated. Using a two-sample *t*-test, the change or percent change at each point in time between the two arms will be compared. The two-sided 95% confidence interval for average difference between the two arms will be estimated. If the data is found to be non-normal, use of nonparametric methods and statistical methods based on probability distribution other than normal distribution will be considered. With regard to binary endpoints, a contingency table will be compiled for each point in time, and Fisher’s exact test will be applied in making comparison of the distribution in the two dosage arms. The Clopper-Pearson method will be applied to estimate the two-sided 95% confidence interval for each dosage arm. The difference in the two-sided 95% confidence interval will be estimated using the normal approximation.

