## Target Study Sample Size

A sample size of 16 subjects is expected to be studied: 12 subjects for NPC-12T active substance arm, and 4 subjects for NPC-12T placebo arm.

[Reason for choice of sample size]

As this clinical trial will focus on a rare disease, and is exploratory, feasibility was the main aspect that was considered in setting the sample size. In terms of safety analysis, provided that clinically significant adverse events exist, the size is sufficient to detect adverse events of 15% incidence with 85% accuracy. In terms of efficacy analysis, when making a comparison of NPC-12T arms concerning hearing test endpoints of periods without treatment and with treatment, a difference can be detected at 80% power (two-sided 5% significance level), if the number of evaluable subjects is 11 and Cohen’s d for endpoints is 0.85.

In estimation of correlation coefficient between evaluation indices, if data of two arms are integrated for evaluation, and the number of evaluable subjects having population correlation coefficient of 0.7 (i.e., medium to high degree of correlation) is 13, then a difference can be detected at a minimum of 80% power (two-sided 5% significance level).

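### Balance is listed only as a yes/no worsening endpoint compared by Fisher's exact test in 12 v 4 subjects; no listed endpoint uses a balance measurement on its continuous scale

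*Protocol*

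**What the plan says.** Section 17.3.1, the synopsis and the Endpoints section list nine secondary efficacy endpoints. The one on equilibrium is number 9: "Percentage of cases in which equilibrium exacerbated during remission in the observation period", determined by "comparison of measurements at the end of Phase I and the end of Phase II". Each subject is therefore classified as worsened or not.

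Section 17.3 fixes the methods by type of endpoint:

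- **Binary:** "Fisher’s exact test will be applied in making comparison of the distribution in the two dosage arms", with a Clopper-Pearson interval for each arm and a normal-approximation interval for the difference.
- **Continuous:** a one-sample t-test and a 95% interval for the mean change within each arm. By two-sample t-test, "the change or percent change at each point in time between the two arms will be compared", with a 95% interval for the difference.

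Hearing has endpoint 5 (percentage with an increased threshold) and also endpoint 6, "Improvement in threshold during remission". Section 17.5 sets the arms: "12 subjects for NPC-12T active substance arm, and 4 subjects for NPC-12T placebo arm". Section 17.6 sets a two-sided 5% level with no multiplicity adjustment. Under section 14.7.7, posturography is recorded at V0, V1, V3, V4, V5 and V7 to V13 (12 scheduled visits) and at discontinuation.

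**The concern.** A balance test yields a number, and a yes/no classification keeps only which side of a cut that number falls on. With 4 placebo subjects, Fisher's test has very few tables that can reach significance, so the loss is larger than it would be in a bigger trial.

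The protocol avoids this for hearing by pairing endpoint 5 with endpoint 6, but gives balance no such partner and no reason for the difference. As a binary endpoint, number 9 also gets no within-arm before-after test under 17.3; it gets only an interval for the proportion.

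The background section on problems in clinical development says the trial will explore which tests allow the most precise evaluation. A mean change with its interval serves that aim better than a count of worsened subjects.

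**Working it through.** **The plan's own power figure.** Section 17.5 states 80% power for n = 11 and d = 0.85. This is for hearing endpoints, comparing untreated and treated periods. The normal approximation reproduces it: Φ(0.85 × √11 − 1.96) = Φ(0.859) = 80.5%. The exact one-sample t-test gives 72.0%. No power, effect size or event rate is stated for balance.

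**Inputs.** Arms of 12 and 4 (17.5); two-sided 5% (17.6); Fisher's test for binary and the two-sample t-test for continuous endpoints (17.3).

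**Assumptions, not in the protocol.** Change scores are normal with equal SD. The standardised difference between arms, d, is 0.85 (borrowed from hearing), 1.5 or 2.0. The placebo worsening rate, p0, runs from 30% to 80%.

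**When Fisher's test can reject in favour of active.** All 13 × 5 tables were enumerated.

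- Placebo 4/4 rejects with 0 to 3 of 12 worsened on active.
- Placebo 3/4 rejects with 0 or 1 of 12.
- Placebo 2/4 against 0/12 gives p = C(4,2)/C(16,2) = 6/120 = 0.05 exactly. Whether it counts depends on using p < 0.05 or p ≤ 0.05.

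The maximum true size is 1.1% under p < 0.05 and 2.0% under p ≤ 0.05.

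**t-test power.** Noncentral t with 14 df and noncentrality d × √(12 × 4/16) = d × √3, that is 1.47, 2.60 and 3.46.

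**Fisher power.** Active rate p1 = Φ(Φ⁻¹(p0) − d). For example, p0 = 50% and d = 0.85 give p1 = Φ(−0.85) = 19.8%. Power is the sum of the two binomial probabilities over all rejecting tables.

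| d | t-test | Fisher, rejecting if | p0 = 30% | 40% | 50% | 60% | 70% | 80% |
|---|---|---|---|---|---|---|---|---|
| 0.85 | 27.9% | p < 0.05 | 6.3% | 10.1% | 12.0% | 11.4% | 8.2% | 3.3% |
| | | p ≤ 0.05 | 15.5% | 16.2% | 14.7% | 12.1% | 8.3% | 3.3% |
| 1.5 | 67.6% | p < 0.05 | 8.2% | 16.7% | 26.5% | 34.3% | 37.1% | 32.0% |
| | | p ≤ 0.05 | 28.6% | 37.9% | 42.8% | 43.3% | 40.2% | 32.5% |
| 2.0 | 89.6% | p < 0.05 | 8.4% | 17.8% | 30.5% | 44.7% | 56.6% | 61.6% |
| | | p ≤ 0.05 | 33.0% | 47.6% | 59.0% | 65.8% | 67.7% | 64.7% |

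**Relative loss, 1 − Fisher/t-test.**

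- d = 0.85: from 1 − 16.2/27.9 = 42% to 1 − 3.3/27.9 = 88%.
- d = 1.5: from 1 − 43.3/67.6 = 36% to 1 − 8.2/67.6 = 88%.
- d = 2.0: from 1 − 67.7/89.6 = 24% to 1 − 8.4/89.6 = 91%.

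**Limiting case.** Suppose nobody on active worsens and p0 = 50%. Under p < 0.05, Fisher's power is P(3 or 4 of 4) = 5/16 = 31%. Under p ≤ 0.05 it is P(2, 3 or 4 of 4) = 11/16 = 69%.

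**The case against.** The case for leaving the plan as it is has several sound parts.

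- **The measure is not named.** A reader might take endpoint 9 to be posturography cut at a threshold. The protocol does not say so. Caloric and c-VEMP tests are also done at V5 and V12, and home devices run throughout, so worsening could be a judgement over several tests. The calculation above then only illustrates the cost of a yes/no scale.
- **The data are not thrown away.** A reader might infer that the posturography measurements are discarded. They are recorded on the case report forms, and 17.5 also foresees correlations between evaluation indices with the arms pooled. What the text supports is that no listed endpoint uses them on their own scale.
- **The fate of posturography does not hang on one p-value.** A reader might infer that the trial could dismiss it as an outcome measure on this test. No section makes that decision rule.
- **Half or more of the power is not always lost.** With a favourable cut and p = 0.05 counted, the loss is 36% at d = 1.5 and 24% at d = 2.0.
- **The gain is limited.** The t-test has only 28% power at d = 0.85 and needs d of about 1.74 for 80%. The main constraint is the 4 placebo subjects, chosen for feasibility. Efficacy is secondary and unadjusted, and endpoints 4 and 8 already give continuous data on nystagmus and dizziness handicap.
- **The SAP may add more.** Section 17.9 defers detail to a statistical analysis plan, which is not at hand.

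The last point does not dispose of the matter. The protocol itself fixes both the scale of endpoint 9 and the test for it, and under 17.8 a different method would have to be reported as a change. Nystagmus and a patient-reported handicap score do not replace a measurement of equilibrium. The other points narrow the claim without removing it.

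**Conclusion.** The point holds in limited form. Equilibrium is the subject of one listed endpoint, that endpoint is binary, and 17.3 compares it by Fisher's test at 12 v 4. Power was below that of a t-test on the change at every effect size and placebo rate tried, by anything from about a quarter to about nine tenths.

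That range rests on normal change scores, equal SDs and effect sizes and rates that the protocol does not supply for balance. It also depends on how a p-value of exactly 0.05 is treated.

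The consequence is moderate. It concerns a secondary, exploratory endpoint for which no power is claimed, and a continuous analysis would still be weak between arms at moderate effects. Its more useful product would be interval estimates, within and between arms, on a measured scale.

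**What to change.** In 17.3.1, the synopsis and the Endpoints section:

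1. Name one equilibrium measure in advance, for example one posturography parameter.
2. Define the endpoint as its change during remission from the end of Phase I to the end of Phase II.
3. Analyse it with the continuous-endpoint methods already in 17.3: mean change within each arm and the difference between arms, each with a 95% interval, on a log or rank scale if the data are skewed.
4. Keep the percentage exacerbated as a descriptive result with Clopper-Pearson intervals.

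The cost is wording in three places of the protocol, matching SAP text and one more table. If the named measure is one already recorded at both time points, no visit, test or subject is added. The small downside is having to commit to one parameter beforehand.

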## Statistical Analysis of Safety

### Adverse Events

The number of occurrences and types of adverse events and of side effects will be sorted by clinical symptoms and by abnormal change of clinical test results. A two-sided 95% confidence interval of the incidence rate by respective dosing arms will be calculated using the Clopper-Pearson method.

### Clinical Test Results and Vital Signs

With regard to continuous endpoints, actual measurements, summary statistics of amounts or rates of change, and two-sided 95% confidence intervals will be calculated for each dosing arm. With regard to discrete variables, cross tables of baselines and individual time points will be created for each dosing arm.

## Target Study Sample Size

A sample size of 16 subjects is expected to be studied: 12 subjects for NPC-12T active substance arm, and 4 subjects for NPC-12T placebo arm.

[Reason for choice of sample size]

As this clinical trial will focus on a rare disease, and is exploratory, feasibility was the main aspect that was considered in setting the sample size. In terms of safety analysis, provided that clinically significant adverse events exist, the size is sufficient to detect adverse events of 15% incidence with 85% accuracy. In terms of efficacy analysis, when making a comparison of NPC-12T arms concerning hearing test endpoints of periods without treatment and with treatment, a difference can be detected at 80% power (two-sided 5% significance level), if the number of evaluable subjects is 11 and Cohen’s d for endpoints is 0.85.

In estimation of correlation coefficient between evaluation indices, if data of two arms are integrated for evaluation, and the number of evaluable subjects having population correlation coefficient of 0.7 (i.e., medium to high degree of correlation) is 13, then a difference can be detected at a minimum of 80% power (two-sided 5% significance level).

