| 1. Target Study Sample Size   A sample size of 16 subjects is expected to be studied: 12 subjects for NPC-12T active substance arm, and 4 subjects for NPC-12T placebo arm.  [Reason for choice of sample size]  As this clinical trial will focus on a rare disease, and is exploratory, feasibility was the main aspect that was considered in setting the sample size. In terms of safety analysis, provided that clinically significant adverse events exist, the size is sufficient to detect adverse events of 15% incidence with 85% accuracy. In terms of efficacy analysis, when making a comparison of NPC-12T active substance arm concerning hearing test endpoints of periods without treatment and with treatment, a difference can be detected at 80% power (two-sided 5% significance level), if the number of evaluable subjects is 11 and Cohen’s d for endpoints is 0.85.  In estimation of correlation coefficients between evaluation indices, if data of two arms are integrated for evaluation, and the number of evaluable subjects having population correlation coefficient of 0.7 (i.e., medium to high degree of correlation) is 13, a difference can be detected at a minimum of 80% power (two-sided 5% significance level). |
| 1. Expected Duration of the Study   From March 2018 to November 2020 (approximately 2.5 year) (Registration: From March 2018 to December 2019 (approximately 22 months)) |

|  | Screening | Phase I (3 months) | | | | Phase II (6 months) | | | | | | | | Follow-up | Discontinuation |
| --- | --- | --- | --- | --- | --- | --- | --- | --- | --- | --- | --- | --- | --- | --- | --- |
| **Visits** | Visit 0 (V0) | V1 | V2 | V3 | V4 | V5^1,2^ | V6^2^ | V7^2^ | V8 | V9 | V10 | V11 | V12 | V13 |  |
| **Days/Week** | -2W | D1 | 2W | 4W | 8W | 12W | 14W | 16W | 20W | 24W | 28W | 32W | 36W | 40W |  |
| **Allowable visit windows (days)** | +/-7 | 0 | +/-3 | +/-3 | +/-7 | +/-3 | +/-3 | +/-3 | +/-7 | +/-7 | +/-7 | +/-7 | +/-7 | +/-7 |  |
| In-clinic visits | X | X | X | X | X | X | X | X | X | X | X | X | X | X | X |
| Informed consent | X |  |  |  |  |  |  |  |  |  |  |  |  |  |  |
| Eligibility judgment, random assignment, and prescription of investigational products | | | | | | |  |  |  |  |  |  |  |  |  |
| Eligibility judgment | X | X |  |  |  |  |  |  |  |  |  |  |  |  |  |
| Registration and assignment |  | X |  |  |  |  |  |  |  |  |  |  |  |  |  |
| Prescription of investigational products |  | X | X | X | X | X^1^ | X | X | X | X | X | X |  |  |  |

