## Significance Level and Multiplicity

The level of significance used for all analyses in this trial is to be two-sided 5%. The confidence coefficient of confidence interval is to be two-sided 95%. As the efficacy analysis in this trial is for a secondary purpose, multiplicity of different endpoints and time points will not be adjusted.

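### The 80% power stated for 11 evaluable subjects at d = 0.85 is about 72% for the planned one-sample t-test, if d is the standardised within-subject change

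*Protocol*

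**What the plan says.** Section 17.5 of the protocol, Target Study Sample Size, claims "80% power (two-sided 5% significance level), if the number of evaluable subjects is 11 and Cohen’s d for endpoints is 0.85". The synopsis gives the same figures. The two places describe the comparison differently. The synopsis has "when making a comparison of NPC-12T active substance arm concerning hearing test endpoints of periods without treatment and with treatment", while Section 17.5 has "when making a comparison of NPC-12T arms concerning hearing test endpoints of periods without treatment and with treatment".

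Section 17.3, Statistical Analysis of Efficacy, plans a one-sample t-test for change within an arm, which "will be used for comparison between actual measurements and baseline values at each point in time for each dosage arm". Section 17.6 sets a two-sided 5% level for every analysis. The planned arms are 12 active and 4 placebo.

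The protocol names no formula for the power and does not say which standard deviation scales d. It does say that the trial is exploratory, that feasibility was the main consideration for its size, and that efficacy is a secondary objective.

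**The concern.** With 11 subjects a t-test has only 10 degrees of freedom, and its critical value is clearly larger than 1.96. A power calculation that ignores this is optimistic by several points. The combination of 11 subjects, d = 0.85 and 80% is what the normal formula gives, so it looked as though the power had been worked out for a z-test while the analysis section plans a t-test.

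What is at stake is interpretation. A non-significant within-arm result would be read as coming from a test with a 20% chance of missing an effect of d = 0.85, when the chance would be 28%. Readers planning the next trial from this one would also take 0.85 as the effect that this size could detect with 80% power, which understates it.

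**Working it through.** **Inputs**
- Two-sided alpha 0.05 (Sections 17.5 and 17.6).
- n = 11 evaluable subjects and d = 0.85 (Section 17.5 and synopsis); 12 subjects planned in the active arm.
- Test: one-sample t-test on change from baseline within an arm (Section 17.3). A paired comparison of two periods in the same subjects is the same test applied to the differences.
- Assumption: d is the mean within-subject change divided by the SD of that change. The protocol does not define it.

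**Reproducing the stated figure**

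Normal approximation: power = Φ(d√n − 1.960).

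0.85 × √11 = 2.819, and 2.819 − 1.960 = 0.859, so power = Φ(0.859) = 80.5%.

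The inverse formula gives n = ((1.9600 + 0.8416)/0.85)² = (2.8016/0.85)² = 10.86, rounded up to 11. Both the 11 and the 80% come out. A one-sided t-test at n = 11 would give 83.6%, but the text says two-sided.

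**Power of the planned test**

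Exact power = P(|T| > t₀.₉₇₅,ₙ₋₁), where T is noncentral t with n − 1 degrees of freedom and noncentrality d√n.

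| n | df | critical t | 0.85√n | power |
| --- | --- | --- | --- | --- |
| 11 | 10 | 2.228 | 2.819 | 72.0% |
| 12 | 11 | 2.201 | 2.944 | 76.4% |
| 13 | 12 | 2.179 | 3.065 | 80.3% |

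A simulation of 200,000 trials with n = 11 and normal data gave 72.1%. Solving for n at 80% gives 12.9, so 13 subjects.

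**Effect detectable at 80% power**

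Solving the same expression for d gives 0.94 with 11 subjects and 0.89 with 12.

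**Sensitivity to the meaning of d**

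If d were scaled by the raw between-subject SD, with equal SDs in the two periods and within-subject correlation ρ, the standardised change would be 0.85/√(2(1 − ρ)). The documents give no ρ, so it is varied here at n = 11:

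| ρ (assumed) | power |
| --- | --- |
| 0.3 | 58% |
| 0.5 | 72% |
| 0.6 | 81% |
| 0.7 | 91% |

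On this reading, 80% requires 1 − (0.85/0.938)²/2, which is about 0.59, where 0.938 is the unrounded form of the 0.94 above.

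**The case against.** The strongest reply is that little depends on the figure. The primary endpoints are safety and tolerability, efficacy is secondary and unadjusted for multiplicity, and feasibility governed the size. No success criterion uses the 80%. All of this stands and limits the weight of the point, but it does not make the stated power correct.

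A second reply is that d is undefined and that a raw-SD scaling could restore 80%. That is arithmetically true, but it needs a correlation of about 0.59 that the protocol never states. For a one-sample t-test on change, the SD of the change is the natural scale. What stands is that 72% is conditional on that reading, and the corrected text must define d.

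A third reply is that Section 17.3 compares each time point with baseline, whereas the power sentence compares periods, and details of the period comparison may sit in the statistical analysis plan. That is a fair caution about the match. An ordinary paired t-test on period values would still have the same 72%, and the power figure itself is fixed in the protocol.

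Two stronger readings are tempting. Seeing the plural arms in Section 17.5, a reader might infer that the claim covers active against placebo and is far more wrong still. The text does not support this: the same sentence contrasts periods without and with treatment, and the synopsis names the active arm, so the plural is a wording slip. A reader might also infer that this is the only efficacy power in the protocol. It is not, since the next paragraph gives one for correlations between evaluation indices with 13 evaluable subjects.

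**Conclusion.** The point holds as a correction to a stated figure. With d read as the standardised within-subject change, the planned two-sided one-sample t-test has 72.0% power for d = 0.85 with 11 subjects, 8 points below the claim. Even if every active subject is evaluable, power is 76.4%. The claimed 80% needs 13 subjects, more than the 12 in the arm.

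The normal approximation is the likely origin because it returns both 11 and 80.5%. This is an inference, since no formula is given, and the shortfall does not depend on it. The calculation assumes normally distributed changes.

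A reader might conclude that the trial is too small or the design unsound. The documents do not support that, because the size rests on feasibility in a rare disease and no decision rule uses this power. The sentence should be corrected; the design can stay as it is.

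**What to change.** In Section 17.5 and the synopsis, replace the efficacy power sentence with wording to this effect: *With d defined as the mean within-subject change divided by its standard deviation, 11 evaluable subjects in the active substance arm give the two-sided 5% one-sample t-test 72% power for d = 0.85 (76% with 12 subjects); 80% power corresponds to d = 0.94 (0.89 with 12). This comparison is within-arm and uncontrolled.*

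Name the active substance arm in both places so that the two descriptions agree. If the sponsor intended a different scaling of d, the text should state it together with the within-subject correlation assumed.

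The cost is about two sentences in each place and a less favourable published figure. Enrolment, endpoints and tests do not change.
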